### Anthropometry and body composition

Height is measured to the nearest 0.1 cm with a wall stadiometer (SECA®, Hamburg, Germany), following the Directorate-General for Health protocol [24]. Participants remove their clothes, socks, and any metal objects prior to measurement of body weight and body composition (including percentage of fat mass, fat mass, fat-free mass and skeletal muscle mass) by tetrapolar bioimpedance (Inbody®, model 770, Seoul, Korea). Body mass index is also obtained by the device report and percentage of excess weight loss is calculated as: $$\frac{\mathrm{baseline\,weight}\left(\mathrm{kg}\right)-\mathrm{follow\,}-\mathrm{\,up\,weight}\,(kg)}{\mathrm{baseline\,weight}\left(\mathrm{kg}\right)-\mathrm{ideal\,weight\,for\,BMI\,}25\mathrm{\,kg}/\mathrm m^2}\times100$$ [25]. Weight and body composition is measured at all visits.

### Gastrointestinal quality of life

Previous studies have shown that the administration of probiotics may improve symptomatic gastrointestinal episodes after gastric bypass surgeries and improve quality of life [26, 27]. Therefore, to assess the gastrointestinal quality of life before and after intervention participants fill out a self-reported questionnaire [Gastrointestinal Quality of Life Index (GIQLI)] at all visits. GIQLI questionnaire includes 36 items divided between five domains: symptoms, physical dysfunction, emotional dysfunctions, social dysfunction, and effect of treatment. The total score is computed as the sum of the response option to each of the 36 items, ranging from 0 (least desirable option) to 4 points (most desirable option). The total score is the sum of item points and ranges from 0 to 144, with higher scores indicating more favourable conditions [28].

### Dietary intake

Dietary intake in the previous 12 months is evaluated by a validated food frequency questionnaire [29] at baseline. Throughout the trial, between visits 2 and 5, subjects complete 2-day food records to describe all foods and fluids consumed in detail including brand names, types of foods and culinary methods. Quantities are described using standard household measures and the information from food labels (where appropriate). A trained dietitian gives the standardised instructions for completing the food diaries and is also responsible for reviewing each record with the participants to clarify errors, omissions, questionable entries, or unclear descriptions. These dietary records will be entered into Food Processor SQL software V.11.1 (ESHA Research, Salem, OR, USA) also by a trained dietitian.

### Glycaemic control, lipid profile, and other blood tests

Routine parameters, including fasting blood glucose, insulin, glycated haemoglobin, c-peptide, triacylglycerides, total cholesterol, high-density lipoprotein (HDL) cholesterol, low-density lipoprotein (LDL) cholesterol, very-low-density lipoprotein (VLDL) cholesterol, alanine transaminase, aspartate transaminase, alkaline phosphatase, gamma-glutamyl transpeptidase, vitamins and minerals (iron, calcium, zinc, copper, magnesium, vitamin B6, vitamin B12, 25-hydroxy-vitamin D) are measured by an outsourced certified medical laboratory. Insulin resistance and sensitivity, and β-cell function are estimated by Homeostatic Model Assessment (HOMA) [30]. GLP-1 (Glucagon Like Peptide 1 (Active) ELISA, Merck®, Darmstadt, Germany) and gastric inhibitory polypeptide (GIP) (Human GIP (total) ELISA, Merck®, Darmstadt, Germany) are measured by ELISA procedure.

### Gut microbiota composition and gut metabolites

Genomic DNA will be extracted and purified from faecal samples using NZY Tissue gDNA Isolation Kit (NZY Tech, Lisboa, Portugal), as described by Marques et al. [31]. Whole-metagenome shotgun sequencing will be performed on the Illumina HiSeq3000 platform to characterize gut microbiota composition as previously described [32, 33]. Gut metabolites [short-chain fatty acids (acetate, propionate, and butyrate), trimethylamine N-oxide, indole-3-propionic acid and imidazole propionate] will be evaluated by targeted metabolomics in serum and faecal samples [34]. ClpB will be assessed in serum and faecal samples by ELISA [Human Caseinolytic peptidase B protein homolog (CLPB) ELISA Kit (MyBioSource, San Diego, CA, USA)], according to manufacturer’s procedures.

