It is known that changes in gut microbiota after bariatric surgery play a pivotal role on the beneficial effects related to this surgical intervention, including appetite regulation [6]. In fact, as shown in a clinical study from our group that involved subjects with type 2 diabetes and excess weight [7], gut microbiota changes towards eubiosis preceded glycaemic improvements, demonstrating the important role that the gut microbiome has on metabolic control. Furthermore, previous studies have shown that preoperative gut microbiota composition is a good predictor of bariatric surgery outcomes, including weight loss trajectory [8, 9]. Nonetheless, recent studies indicate that gut microbiota eubiosis is not fully restored after bariatric surgery [6] and that subjects that regained weight have significantly different gut microbiota in comparison to more successful postoperative settings [10]. Hence*,* strengthening the restoration of gut microbiota with probiotics possibly promoting appetite control may be important to improve the metabolic outcomes and weight loss after surgery. Recently, the strain *Hafnia alvei*, a commensal bacterium that belongs to the Hafniaceae family (formerly Enterobacteriaceae), has raised interest regarding its mechanism of action in appetite control [11]. *Hafnia alvei* can synthesize caseinolytic protease B protein (ClpB), which was identified as a conformational antigen mimetic of α-melanocyte-stimulating hormone [11]. ClpB stimulates glucagon-like peptide-1 (GLP-1) and peptide YY secretion by L-cells in the gut and can also stimulate other anorexigenic pathways in the hypothalamus by activating proopiomelanocortin (POMC) neurons [12]. In addition, activation of POMC neurons increases lipolysis and contributes to lowering glucose levels through leptin signalling pathway [11, 13]. Interestingly, gut microbiota of individuals with obesity have low abundance of enterobacterial ClpB [12], which can contribute to appetite dysregulation. Based on these findings, pre-clinical studies were conducted to assess the effect of *Hafnia alvei* as a potential probiotic (*Hafnia alvei* HA4597™) for appetite control and weight management in obese models. Results showed that *Hafnia alvei* HA4597™ supplementation decreased appetite and had anti-obesity and anti-diabetic effects in animal models of obesity [11, 14]. These results were confirmed afterwards in a multicentric, double-blind, randomized, placebo-controlled trial that included 236 overweight subjects, successfully demonstrating the use of *Hafnia alvei* HA4597™ in weight and glycaemic control management [15]. Nevertheless, validation of the effect of *Hafnia alvei* HA4597™ in subjects with obesity is still required, particularly in more severe cases as an adjuvant therapy for bariatric surgery and, possibly, exploring other complementary mechanisms as consequence of gut microbiota modulation, including systemic inflammation and metabolites produced by gut bacteria with relevant metabolic impact. This could contribute to improvement of weight and glycaemic management of subjects with obesity in the long-term and to a better understanding of the role of gut microbiota as therapeutic target in obesity.

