
## Study objectives

The purpose of this paper is to describe the RESTART project protocol. A study that aims to understand the link between dysbiosis and obesity, assessing the effect of *Hafnia alvei* HA4597™ supplementation as an adjuvant treatment in the context of bariatric surgery for weight loss and glycaemic control. In this regard, the specific aims of this trial are:

Primary aims:To evaluate if *Hafnia alvei* HA4597™ supplementation improves the percentage of excess weight loss.To assess the impact of *Hafnia alvei* HA4597™ supplementation on glycated haemoglobin (HbA1c).

Secondary aims:To evaluate the effect of *Hafnia alvei* HA4597™ supplementation on fasting glucose, HOMA-IR, HOMA-S, HOMA-B, and c-peptide.To analyse the effect of *Hafnia alvei* HA4597™ supplementation on gut microbiota composition.To analyse the effect of HA4597™ supplementation on gut metabolites: ClpB, short-chain fatty acids (acetate, propionate, and butyrate), trimethylamine N-oxide, indole-3-propionic acid, imidazole propionate.To evaluate if *Hafnia alvei* HA4597™ supplementation can improve gastrointestinal quality of life.

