### Secondary outcomes

As secondary outcomes, the impact of *Hafnia alvei* HA4597™ supplementation will be assessed towards changes in gut microbiota composition, including diversity, richness, and characterization of microbes at phylum, class, order, family, genus, and species level at baseline, and 3, 6, 9, and 12 months. Alterations in the metabolites produced by gut microbiota that have already demonstrated a protective or a deleterious effect in obesity and type 2 diabetes conditions, namely short-chain fatty acids (acetate, propionate and butyrate), trimethylamine N-oxide, indole-3-propionic acid, imidazole propionate [18–21], will also be determined at the same timepoints. Another important gut metabolite that will be assessed is ClpB, which is specifically produced by *Hafnia alvei* strain and is related to its recognized metabolic effect on appetite regulation [22]. Changes in ClpB levels will be determined before (baseline and 3 months) and after the intervention (6, 9, 12 months).

Additionally, the trial will assess the effect of supplementation on inflammatory markers, including calprotectin, zonulin, c-reactive protein, lipopolysaccharides, transforming growth factor-β, monocyte chemoattractant protein-1, interferon gamma, IL-1 β, IL-6, IL-10, and on other important metabolic outcomes, such as fasting glucose, HOMA-IR, HOMA-S, HOMA-B, and c-peptide, total cholesterol, HDL cholesterol, LDL cholesterol, VLDL cholesterol and triacylglycerides, and vitamins and minerals status (iron, calcium, zinc, copper, magnesium, vitamin B6, vitamin B12, 25-hydroxy-vitamin D) on all visits. GLP-1 and GIP will also be determined at all visits. Lastly, gastrointestinal quality of life impact will be assessed at baseline, and 3, 6, 9, and 12 months.

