## Discussion

Gut microbiota modulation after bariatric surgery could be one missing key towards restoring the dysbiotic state reminiscent of an obese-related environment. Re-establishing this imbalance with adequate probiotics may trigger satiety pathways and contribute to anti-inflammatory effects, directly and/or indirectly enhancing bariatric surgery success, including weight loss and glycaemic response management. Past studies that assessed the effect of probiotics on weight loss in humans have been more focused in strains of *Lactobacillus* and *Bifidobacterium* genera [41]. However, the impact of probiotic supplementation after bariatric surgery has shown to be very inconsistent, appearing to be dependent on the type of probiotic, duration of consumption, time of follow-up, and typology of bariatric procedure [26]. This said, well-designed randomized placebo-controlled trials are very scarce, and it is necessary to evaluate the effect of probiotics with strain-specific properties based on a better understanding of the mechanisms of action of commensal bacteria on the host. *Hafnia alvei* HA4597™ could be a potential strain to be used as a probiotic after bariatric surgery based on its anti-obesity, satiety-inducing, and lowering glucose and cholesterol effects, which have been pointed out as consequences of increased levels of ClpB production [11, 14, 15]. Although similar effects have been observed in overweight subjects, unravelling the magnitude of the effect of *Hafnia alvei* HA4597™ in obese individuals, especially as a coadjuvant measure for bariatric surgery on weight loss and glycaemic control is warranted. Adding to this, because subjects with obesity exhibit lower ClpB levels [12], contributing to obesity-related metabolic dysfunction, it is important to assess *Hafnia alvei* HA4597™ supplementation in ClpB production on this target group. Likewise, it is crucial to explore its mechanisms of action in humans, understanding its impact on gut metabolites and systemic inflammation. This could contribute to the establishment of a post-surgery protocol that incorporates gut microbiota as a therapeutic target, which may ultimately contribute to a better success of the surgery and improved quality of life for the patients.

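### The ClpB outcome is defined as a bacterial protein made by the supplemented strain, but the named ELISA kit is for the human CLPB homolog, so the ClpB aim may be answered with the wrong analyte.

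*Protocol article*

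**What the plan says.** The Background section says that Hafnia alvei "can synthesize caseinolytic protease B protein (ClpB") and that people with obesity "have low abundance of enterobacterial ClpB". Study objectives makes ClpB part of a secondary aim, the effect of "supplementation on gut metabolites: ClpB, short-chain fatty acids" and further metabolites. Secondary outcomes gives the reason for measuring it: "Another important gut metabolite that will be assessed is ClpB, which is specifically produced by" the Hafnia alvei strain. The same section sets the timing: "Changes in ClpB levels will be determined before (baseline and 3 months) and after the intervention (6, 9, 12 months"). The Discussion refers to the strain's effects on weight, satiety, glucose and cholesterol as ones "which have been pointed out as consequences of increased levels of ClpB production".

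The assay is fixed in the section Gut microbiota composition and gut metabolites. ClpB is to be measured by ELISA in serum and faecal samples, following the manufacturer's instructions, with the "Human Caseinolytic peptidase B protein homolog (CLPB) ELISA Kit". The abbreviation list under Table 1 expands ClpB with the same homolog name, which is not the expansion given in the Background.

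**The concern.** The rationale, the aim and the outcome all concern a protein that comes from bacteria, whereas the kit is named for the human counterpart of that protein. An assay directed at the participant's own protein need not respond to the bacterial one, and the article gives no evidence that this kit does.

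ClpB is more than one line in a long list of biomarkers. It is the proposed link between the capsule and appetite, and the Discussion calls it important to assess the supplement's effect on ClpB production in this population. If the kit reads only the human protein, that question goes unanswered, and no analysis can recover the intended quantity from measurements of a different one.

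**Working it through.** No figure in the plan depends on this point. The sample size rests on excess weight loss and fasting glucose. The check is therefore a comparison of texts.

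**1. What the outcome is meant to be.**
- Background: a protein synthesised by Hafnia alvei; the form said to be scarce in obesity is enterobacterial.
- Secondary outcomes: chosen because the strain produces it.
- Discussion: increased ClpB production is offered as the explanation of the strain's effects.

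The three sections agree that the target is bacterial.

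**2. What the assay is named for.**
- Gut microbiota composition and gut metabolites: the human CLPB homolog.
- Table 1 abbreviation list: the same homolog name, without the word human.

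**3. Whether the word human in the kit name marks the target or only the sample.** Two other kits in the article carry it: the total GIP kit (Glycaemic control, lipid profile, and other blood tests) and the C-reactive protein kit (Lipopolysaccharides and inflammatory markers). Both measure human proteins. The faecal calprotectin and zonulin kits are labelled by matrix instead, and the GLP-1 kit carries no species label. The more natural reading is that human names the target. The word homolog points the same way, because it denotes a counterpart of ClpB. This is an inference from naming. It does not prove antibody specificity.

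**4. Which visits are affected.** ClpB is measured at five visits. Two of them, baseline and 3 months, precede the intervention, so no assay could show an effect there. That leaves 5 − 2 = 3 visits, at 6, 9 and 12 months, at which an intervention effect could appear and at which the choice of analyte decides what it means.

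**5. Range of consequence.** The kit's response to bacterial ClpB is not given.
- Full response with negligible signal from the human protein: nothing is lost.
- Partial response, or response to both proteins: the reading mixes the two in unknown proportion.
- No response: the three comparisons concern the human protein only. A null result leaves bacterial ClpB untested. A difference between arms shows an effect on the human protein.

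**The case against.** The strongest reply is that the point rests on a product name. The article gives no immunogen or cross-reactivity data, its kit names follow no single convention, and assay validation commonly sits in a fuller protocol. This stands as a limit on certainty. A reader might infer that the kit certainly measures the wrong protein, and the documents do not support that. The reply does not remove the mismatch, because the article does not leave the assay open. It names a specific kit whose name conflicts with its own definition of the outcome.

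Other stronger readings are tempting and should be set aside:
- *A positive result could not be credited to the supplement.* This is not so. Allocation is randomised and blinded, and the Intervention section describes the placebo as the same composition without the live bacteria. A true difference between arms in either protein would be attributable to the live strain. What would remain unknown is which protein had changed.
- *All five visits are lost.* Only the three after the intervention can carry an effect.
- *Host protein in serum adds a background signal in both arms.* No section says that the human homolog circulates in serum, so this is an outside assumption and is not relied on here.
- *A null result will be declared a failure of the mechanism.* The article sets no such rule. The supportable statement is that a null result from a human-only assay would not test the mechanism.
- *The trial would have no evidence of bacterial exposure.* Shotgun sequencing to species level is planned at the same five time points and gives a separate faecal view of Hafnia alvei.

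The objection is also right that ClpB is one of many secondary outcomes and that the primary outcomes and safety monitoring do not depend on it.

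**Conclusion.** The concern holds as a mismatch within the article: the outcome is bacterial ClpB, and the named kit is for the human homolog. Whether the kit also detects the bacterial protein cannot be settled from the documents. The possible loss therefore runs from nothing to all information on bacterial ClpB at 6, 9 and 12 months, in serum and in faeces.

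The reach is limited to the secondary ClpB outcome and the mechanistic reading of the trial. The conclusion assumes that human in the kit name describes the target, as it does for the other two kits so named. It should be put right before the assays are run. The article puts the ClpB measurement in the future and describes samples as stored until analysis, so the plan as described leaves time to act.

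**What to change.** Before any stored sample is assayed for ClpB, do one of the following, in this order of preference.

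1. Name, in the section on gut microbiota composition and gut metabolites, an assay directed at enterobacterial ClpB and suitable for serum and faeces. The documents do not show that such an assay can be had, so this has to be established.
2. Keep the named kit only if a spike-recovery check shows that it detects bacterial ClpB in both matrices. The material should be handled outside the blinded team, for example an independent Hafnia alvei preparation, because the study products are coded and the researchers are to stay blinded until the trial is completed.
3. If neither is possible, report the ELISA as human CLPB, and use Hafnia alvei and clpB gene abundance from the planned shotgun sequencing as the faecal bacterial readout. State that this shows gene presence and not protein level, and that it does not replace the serum measurement.

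In every case, reconcile the definition of ClpB across Background, the Table 1 abbreviation list, Secondary outcomes and the assay section.

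The cost is one validation plate or a change of kit. The sequencing is already planned. The real downside is that the serum ClpB outcome may have to be given up if no assay for the bacterial protein works in serum.

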### Lipopolysaccharides and inflammatory markers

Quantification of lipopolysaccharide in serum samples will be performed using the Chromo-Limulus Amoebocyte Lysate (Chromo-LAL) reagent (Associates of Cape Cod, Inc., Falmouth, MA, USA), according to manufacturer’s procedures. Faecal calprotectin and zonulin levels will be measured as surrogate markers of intestinal permeability [35] by ELISA kit (IDK ® Calprotectin (stool) and IDK® Zonulin (stool) ELISA kits; Immundiagnostik, Bensheim, Germany). Moreover, c-reactive protein will also be determined in plasma samples as a marker of systemic inflammation by ELISA kit (Human C-Reactive Protein ELISA Kit; Sigma-Aldrich, St. Louis, MO, USA), according to manufacturer’s protocol. Inflammatory mediators including transforming growth factor-β, monocyte chemoattractant protein-1, interferon gamma, IL-1 β, IL-6, and IL-10 will be measured in plasma samples in batch by bead-based LEGENDplex™ analysis (Biolegend, San Diego, CA, USA)] and reactions will be run in duplicate with a BD FACSCantoII flow cytometer (BD-Biosciences San Jose, CA, USA) as described by Castela et al. [36] in a certified medical laboratory (Laboratório de Imunologia e Imunodeficiências Primárias @ NOVA Medical School, Lisboa, Portugal).

## Sample size

Sample size calculations have considered the outcomes: percentage of excess weight loss and fasting blood glucose levels. Based on previous studies with a population similar to this study, the assumed standard deviation was 10.70 for percentage of excess weight loss [37] and 14.00 mg/dL for fasting blood glucose [38]. To detect a difference of 10.48% [39] in excess weight loss and 11.30 mg/dL [40] in fasting glucose between the intervention and placebo group after 1 year of follow-up, it was determined that 44 participants are required to allow for an 80% power and 95% confidence level. Compensating for possible attrition, 30% additional samples will be recruited, representing a total of 58 participants (29 in each arm — probiotic group and placebo group). Considering that Hospital CUF Tejo receives around 80 patients each year to be submitted to bariatric surgery, of these around 70% are Roux-en-Y gastric bypass, assuming that 29% of the subjects will not be eligible to participate [39], it is anticipated that it will take approximately 18 months to recruit this sample size.

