Some prespecified subgroup analysis will be done based on some confounding variables such as age, gender, diagnosis of type 2 diabetes, etc., for detecting heterogeneity in intervention efficacy across the strata of mentioned variables. However, these subsamples will be compared to the main dependent variables at baseline. Potential confounding variables will be evaluated in each model. Regression models will be used to predict which factors at baseline most contribute to excess weight loss 1 year after the surgery.

Differences will be considered statistically significant when *p* < 0.05. Effect sizes (Cohen d test) will also be assessed to decide whether a clinically relevant effect is found (|d|> 0.50 indicates a medium effect size and |d|> 0.80 indicates a large effect size).

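### The stated 44 participants do not follow from the plan's own inputs: 44 is more than %EWL needs and gives fasting glucose about 74% power, not 80%, on a two-sided 5% test

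*Protocol article*

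**What the plan says.** All figures are in one paragraph of the protocol article, under Sample size.

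- %EWL: "To detect a difference of 10.48% [39] in excess weight loss", where "the assumed standard deviation was 10.70 for percentage of excess weight loss".
- Fasting glucose: "11.30 mg/dL [40] in fasting glucose between the intervention and placebo group after 1 year of follow-up", with an SD of 14.00 mg/dL.
- Result for the two together: "it was determined that 44 participants are required to allow for an 80% power and 95% confidence level".
- Enrolment: "30% additional samples will be recruited, representing a total of 58 participants", that is 29 per arm.

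Elsewhere, the section on randomization gives 1:1 allocation, and Statistical analysis sets the threshold: "Differences will be considered statistically significant when *p* < 0.05". The article does not say whether the tests are one- or two-sided, which formula produced 44, or what loss rate is expected.

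**The concern.** The sentence presents a single total as giving 80% power for two outcomes with different standardized differences. The outcome with the smaller standardized difference must then set the size, and that is fasting glucose. The total should equal the glucose requirement, yet 44 lies between the two requirements and matches neither.

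Fasting glucose is the only glycaemic measure used for sizing, and glycaemic control is one of the trial's two stated purposes. If the glucose comparison is null, a reader who trusts the paragraph will believe that an 11.30 mg/dL difference had an 80% chance of detection with 44 participants. The plan's own inputs give a lower chance.

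**Working it through.** **Inputs** (Sample size, unless noted)

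- %EWL: difference 10.48, SD 10.70, so d = 10.48/10.70 = 0.979.
- Fasting glucose: difference 11.30, SD 14.00, so d = 11.30/14.00 = 0.807.
- "80% power and 95% confidence level"; α = 0.05.
- 1:1 allocation (Randomization, allocation, and blinding).
- Two-sided test: assumed, because sidedness is not stated.

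**Step 1. Try to reproduce 44.** Normal approximation: n per arm = 2 × (1.960 + 0.842)² × (SD/difference)².

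- %EWL: 16.4, so 17 per arm, 34 in total. By the noncentral t: 17.4, so 18 per arm, **36** in total.
- Glucose: 24.1, so 25 per arm, 50 in total. By the noncentral t: 25.1, so 26 per arm, **52** in total.

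Neither outcome gives 44. For glucose, 44 is 6 to 8 participants short. For %EWL it is 8 to 10 more than needed.

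**Step 2. Look for another route to 44.**

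| Variant | %EWL total | Glucose total |
|---|---|---|
| One-sided 5%, normal / t | 26 / 28 | 38 / 40 |
| Two-sided α = 0.025, t | 44 | 62 |
| Two-sided 5%, 90% power, normal | 44 | 66 |
| Paired formula, two-sided 5% | 11 pairs | 15 pairs |

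The two rows that reach 44 do so for %EWL alone, and each contradicts a stated input (95% confidence or 80% power). The paired row was tried because Statistical analysis names a paired test for the group comparison; it does not explain 44. Rank-test corrections come near (42 for %EWL two-sided; 42 to 46 for glucose one-sided), but the article mentions none in the sizing. No variant makes 44 sufficient for glucose on a two-sided test.

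**Step 3. Power with 44 (22 per arm), two-sided 5%.** Normal approximation: power = Φ(d × √(n/2) − 1.960), with √(22/2) = 3.317.

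- %EWL: 0.979 × 3.317 − 1.960 = 1.29, power 90.1%. Noncentral t: **88.8%**.
- Glucose: 0.807 × 3.317 − 1.960 = 0.72, power 76.3%. Noncentral t: **74.4%**.

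One-sided at 5%, 44 would give glucose 83.9% by the t-test.

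**Step 4. What 58 covers.**

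- 44 × 1.3 = 57.2, rounded up to 58 for equal arms. This reproduces.
- 44 remain evaluable up to a loss of 14/58 = 24.1%.
- 52 remain evaluable up to a loss of 6/58 = 10.3%. At 26 per arm, glucose power is 81.4%.
- With no loss (29 per arm), glucose power is 85.6%.
- Only if 30% is meant as the expected loss: 58 × 0.7 = 40.6, so about 20 per arm. Power is then 85.5% for %EWL and 70.1% for glucose.

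**The case against.** Four points deserve weight.

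1. **Sidedness is an assumption.** On a one-sided 5% test, 44 gives glucose about 84% power, so the shortfall depends on reading the test as two-sided. This stands as a caveat. Two-sided is the usual default, however, and one-sided sizing gives 40, so 44 remains unexplained either way.

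2. **The consequence is limited.** Fasting glucose is a secondary outcome. %EWL keeps 89% power at 44 and about 86% even at 40. The trial enrols 58, and glucose holds at least 80% power while 52, in equal arms, are evaluable. Under Statistical analysis, participants lost to follow-up stay in the intention-to-treat analysis and available medical-record data are collected for them, which may keep the evaluable number up. All of this stands. It bears on the size of the problem and leaves the printed claim wrong.

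3. **The attrition allowance.** A reader might infer that 58 is itself an error because dividing by 0.7 gives 44/0.7 = 62.9, or 63. The document does not support that. It adds 30% to the sample and never gives 30% as the expected loss, so 58 is right for what is written. What can be said is how much loss 58 tolerates.

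4. **Joint power.** A reader might also multiply the two powers and report a much lower chance of success on both outcomes. Nothing in the article requires success on both, and nothing supports treating weight loss and glucose as independent, so no such figure belongs here.

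**Conclusion.** The paragraph is wrong as written. On its own differences and SDs, 80% power needs 36 participants for %EWL and 52 for fasting glucose; 44 matches neither and delivers about 89% and 74%. The glucose shortfall at 44 is about 6 percentage points by the t-test and about 4 by the normal approximation. This rests on a two-sided 5% test, equal arms and the printed inputs. The failure to reproduce 44 also holds one-sided; the power shortfall does not.

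The documents do not support the inference that the trial as enrolled is underpowered for glucose. That depends on losses, and the shortfall appears only once they exceed about 10% of the 58. This is a reporting error in the sizing of a secondary outcome. It should be fixed, but it does not undermine the %EWL sizing.

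**What to change.** State whether the tests are one- or two-sided, and replace the claim with the power actually obtained. Suggested text, for two-sided testing:

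> 44 evaluable participants (22 per arm) give 89% power for a 10.48-point difference in mean %EWL and 74% for an 11.30 mg/dL difference in mean fasting glucose (two-sided 5% t-test). 58 randomised participants retain 44 evaluable with up to 24% attrition. With equal arms, fasting glucose has at least 80% power only while 52 or more are evaluable. These powers refer to differences in means and not to the responder outcomes.

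The last sentence is needed because Primary outcomes counts participants who reach at least 50% excess weight loss or an HbA1c below 5.7%, and the sizing gives no power for either count. If 30% is in fact the expected loss, say so and add that about 40 would then be evaluable, with power of about 86% for %EWL and 70% for glucose.

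The cost is a text correction. Enrolment and conduct do not change; the stated power for glucose becomes less favourable.
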